### Definition of the end of the trial

The end of the study is defined as the date when the last randomised participant is due to respond to their 14-week follow-up text message.

## Statistical analysis

There will be two analyses. A descriptive analysis of the internal pilot data and a single effectiveness analysis of the main trial data at end of follow-up of all participants. All analyses will be conducted in STATA V.15 or later (StataCorp, College Station, Texas, USA). Analyses will be described in detail in a Statistical Analysis Plan drafted by the study statisticians and reviewed by the Trial Steering and Data Monitoring and Ethics Committee.

The trial will be reported according to the Consolidated Standards of Reporting Trials guidelines for clinical trials (http://www.consort-statement.org/). Baseline data (sex, age, job role, etc) will be summarised descriptively overall and by randomised arm, both as randomised and as included in the primary analysis. No formal statistical comparisons of baseline data will be undertaken between the trial arms. Continuous measures will be reported as means and SD while categorical data will be reported as counts and percentages. Data will be processed and stored according to the University of York, YTU’s Standard Operating Procedures. Analyses will be conducted following the principles of intention-to-treat with participant’s outcomes analysed according to their original, randomised group, where data are available, irrespective of deviations based on non-compliance, unless otherwise stated.

### Statistical analysis of the SSHeW primary outcome

Although we have based the sample size calculation on detecting a difference in proportions, the primary outcome is the incidence rate of slips over the 14 weeks of follow-up. We propose to use a mixed effects Poisson or negative binomial regression model (as appropriate depending on the presence of overdispersion) to compare this outcome between the two groups, which will give us a more powerful analysis. The regression model will adjust for pertinent baseline covariates such as gender, age, job role and baseline slip rate ascertained from the run-in period. NHS trust will be included as a random effect to account for potential clustering by recruitment site. The number of weeks for which the participant provided weekly slip data and the number of hours worked in those weeks will be accounted for in the model. Point estimates in the form of an incident rate ratio and their associated 95% CIs will be provided.

### Secondary analysis

All secondary outcomes and other important collected data will be summarised descriptively overall and by trial arm.

The incidence rate of falls (both resulting and not resulting from a slip) over 14 weeks will be analysed in the same way as described above for slips. The following outcomes will be analysed using a mixed effects logistic regression adjusting for the same covariates as the primary analysis and NHS trust as a random effect: (i) the proportion of participants who slip at least once over 14 weeks; (ii) the proportion of participants who fall at least once over 14 weeks and (iii) subject to a sufficient number of events, the proportion of participants who experience a fracture over 14 weeks. ORs and their associated 95% CIs will be provided.

Time to first slip and the time to first fall will be calculated. Participants who do not report a slip or fall will be treated as censored at their date of trial exit (completion of follow-up or withdrawal). The proportion of participants yet to experience a slip/fall will be summarised by a Kaplan-Meier survival curve for each group. Time to slip/fall will be analysed using Cox proportional hazards regression, with shared centre frailty and adjusting for the same covariates as in the primary analysis model. HRs and their associated 95% CIs will be provided. The proportional hazards assumption will be evaluated using Schoenfeld residuals.

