### SSHeW study objectives for the pilot phase

To test and refine the recruitment strategies for the study.To check the sample size calculation assumptions by reviewing the proportion of participants who experience a slip in the control group.To check the attrition rate.To explore and address any issues regarding footwear compliance.

Prior to the start of recruitment, the funder and the independent Trial Steering Committee (TSC) agreed the following stop/go criteria for progression to the main trial.Recruit at least 400 participants in 6 months.Eighty per cent of the participants will contribute at least 50% of the follow-up text data (ie, respond to 7/14 weekly postrandomisation text messages).Ninety per cent will respond to at least one postrandomisation text.The slip rate in the control group will be at least 7%.

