### Randomisation

Participants who fulfil the eligibility criteria, provide written consent to take part in the study, complete a baseline questionnaire and return at least 2 weekly texts providing slip data will be eligible for randomisation. Participants will be randomly allocated using the YTU secure web-based randomisation system based on an allocation sequence generated by an independent data systems manager at the YTU, who is not involved in the recruitment of participants. The randomisation will be stratified by NHS Trust, and block randomisation within Trust will be used with variable block sizes. There will be no limit to the size of the block used. This will be dependent on the number of participants to be randomised at the time. Participants will be allocated 1:1 to either the intervention group, to receive a free pair of slip resistant footwear or the waiting list control group who will be asked to wear their own work footwear for the duration of the study and offered a free pair of slip resistant shoes after completing their follow-up. Participants will be randomised at a particular site in batches, according to when sites state they have capacity to order and deliver footwear. Participants will be notified of their group allocation by a text message, email and/or letter from the YTU. We anticipate that the intervention group will receive their shoes within 2 weeks of randomisation.

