## Outcome measures

### Primary outcome measure for the SSHeW trial

The primary outcome in this study is the incidence rate of self-reported slips, not necessarily resulting in a fall or injury, in the workplace over a 14-week period, as reported via weekly text messages. A slip is defined as ’a loss of traction of your foot on the floor surface, which may or may not result in a fall'. Data will be collected via text messages, sent to/from the participant. Participants will be sent 1 weekly text message with the following content (or similar):

SSHeW trial: How many slips did you have at work between DD/MM/20YY and DD/MM/20YY? Please provide a single number (eg, 2) or 0 if you did not slip. Thank you.

To aid reporting of these events, participants will be given a personal paper weekly diary in which to record if they have a slip or fall, and any resultant injuries. This diary will be sent to them at the start of the study. A fall will be defined as ‘an unexpected event in which you come to rest on the ground, floor, or lower level’.

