### Secondary outcome measures for the SSHeW trial

Secondary outcomes will be self-reported by the participant and collected via text or questionnaires sent at baseline, 14 weeks or following the report of the first slip or an injury. They include:The incidence rate of falls resulting from a slip in the workplace over 14 weeks.The incidence rate of falls not resulting from a slip in the workplace over 14 weeks.Proportion of participants who report a slip over 14 weeks.Proportion of participants who report a fall over 14 weeks.Proportion of participants who report a fracture over 14 weeks (numbers permitting).Time to first slip.Time to first fall.EuroQol EQ5D-5L.Cost-effectiveness.

Other important information collected includes:Reason for slip/fall, location of fall, type of flooring and if wet or dry, consequence of slip/fall, that is, superficial wound (bruising sprain, cut, abrasions), fractures and type of fractures; severity of fall; type of footwear worn at time of slip/fall.Number of days off work, due to the slip or fall.Footwear worn at time of first slip.Number of hospital admissions.Number of days in hospital.Compliance and reasons for non-compliance.Any minor injuries resulting from ill-fitting shoes.Style of footwear usually worn.Wear on soles of 45 intervention shoes at 6, 9 and 12 months postrandomisation.Slip resistance of a sample of the current footwear worn by NHS staff.

Copies of the data collection forms are available from the corresponding author.

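### Time to first slip: censoring at trial exit counts unanswered weeks as slip-free, which overstates the slip-free proportions and can bias the hazard ratio if reply rates differ by arm

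*Protocol article*

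**What the plan says.** Secondary analysis in the protocol article fixes the rule for time to first slip and time to first fall. Participants without a reported event "will be treated as censored at their date of trial exit (completion of follow-up or withdrawal"). Kaplan-Meier curves and a Cox model with shared centre frailty follow from these times.

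The primary outcome is the "incidence rate of self-reported slips, not necessarily resulting in a fall or injury, in the workplace over a 14-week period", collected by one text message a week. Its model (Statistical analysis of the SSHeW primary outcome) takes account of unanswered weeks by including "The number of weeks for which the participant provided weekly slip data" together with the hours worked in those weeks. Secondary outcomes, which include both times to first event, are "collected via text or questionnaires sent at baseline, 14 weeks or following the report of the first slip or an injury".

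On reply rates, the pilot progression criteria include "Eighty per cent of the participants will contribute at least 50% of the follow-up text data" and "Ninety per cent will respond to at least one postrandomisation text". The article gives no reply rates by arm.

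**The concern.** The bracketed definition of trial exit names two routes, and ceasing to reply is neither of them. Nothing in the article treats non-reply as withdrawal. Completion appears to follow the calendar: the end of the trial is set by the date on which the last participant is due to answer the final text, not by an answer received. Read as written, someone who falls silent in week 3 and never withdraws contributes 14 slip-free weeks to the Cox model, although the primary model would credit only the weeks with data.

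Unobserved time counted as event-free pulls the estimated slip risk down in both arms. If one arm falls silent more than the other, its hazard is pulled down more and the hazard ratio moves with it. Different reply behaviour is plausible here. The trial is open, the intervention arm expects shoes within about two weeks, and controls are "offered a free pair of slip resistant shoes after completing their follow-up". Participant recruitment also reports that, before randomisation, some people thought they need not answer texts until their shoes had arrived. The direction cannot be predicted from this.

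**Working it through.** **Inputs.** From the protocol article: 14 weeks of follow-up, 2200 per arm, 10% of controls slipping, a 30% relative reduction (Sample size). Assumed, because the article gives no figures: the share *s* of each arm that goes silent without withdrawing, a uniform time of going silent, and silence unrelated to slip risk.

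**Check of the plan's own figures.** The article gives no figure for the time-to-event analysis. Its sample size inputs do reproduce. With 2200 × 0.8 = 1760 per arm and two-sided 5% (assumed), power is 89.1% for 10% v 7% (stated 90%) and 81.7% for 5.5% v 3.5% (stated 80%). This point does not touch them.

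**Kaplan-Meier level.** If nobody is censored before week 14, the Kaplan-Meier estimate is the observed proportion. A silent participant is observed for half the period on average, so the fraction of person-time observed is 1 − s/2. With s = 20% in both arms: 10% × (1 − 0.20/2) = 9.0%. Counting in whole weeks (last reply uniform on weeks 0 to 13, mean 6.5), the fraction is 1 − s + s × 6.5/14 = 0.893, giving 8.9%. The curves show about 91% slip-free where 90% is true.

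**Hazard ratio.** For infrequent events, the HR under exit censoring ≈ true HR × (observed fraction, intervention ÷ control). With a true HR of 1 and 1 − s/2:

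- silent 10% control / 20% intervention: 0.90/0.95 = 0.95
- 20% / 10%: 0.95/0.90 = 1.06
- 10% / 30%: 0.85/0.95 = 0.89
- 30% / 10%: 0.95/0.85 = 1.12
- equal rates: 1.00

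**Simulation.** Weekly data, 100,000 per arm, constant hazard giving 10% in controls, permanent silence from a uniform week. The approximation uses the whole-week fraction.

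| True HR | Silent control / intervention | Approximation | Cox, exit | Cox, last reply | Exit ÷ last reply |
|---|---|---|---|---|---|
| 1.00 | none | 1.000 | 1.009 | 1.009 | 1.000 |
| 1.00 | 20% / 20% | 1.000 | 0.998 | 0.998 | 1.000 |
| 1.00 | 10% / 20% | 0.943 | 0.952 | 1.011 | 0.942 |
| 1.00 | 20% / 10% | 1.060 | 1.079 | 1.016 | 1.062 |
| 1.00 | 10% / 30% | 0.887 | 0.886 | 0.999 | 0.887 |
| 1.00 | 30% / 10% | 1.128 | 1.115 | 0.987 | 1.130 |
| 0.70 | 20% / 20% | 0.700 | 0.725 | 0.725 | 1.000 |
| 0.70 | 10% / 20% | 0.660 | 0.674 | 0.715 | 0.943 |
| 0.70 | 20% / 10% | 0.742 | 0.754 | 0.710 | 1.062 |
| 0.70 | 10% / 30% | 0.621 | 0.612 | 0.691 | 0.886 |
| 0.70 | 30% / 10% | 0.789 | 0.801 | 0.709 | 1.130 |

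The last column compares the two rules on the same simulated data, so most of the simulation noise cancels. It shows a shift of about 6% for a 10-point difference in silence and 11-13% for a 20-point difference, in either direction. Censoring at the last reply gives 0.99-1.02 for a true 1.00 and 0.69-0.73 for a true 0.70. The 0.725 under equal silence is identical under both rules, so the censoring rule does not cause it.

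**Relative to precision.** With a true HR of 1 and 10% / 20% silent, expected events are 220 × 0.95 + 220 × 0.90 = 407, and SE(log HR) ≈ 2/√407 = 0.10. The shift, ln 0.947 = −0.054, is about half a standard error. At 10% / 30% it is ln 0.895 = −0.111, with 220 × 0.95 + 220 × 0.85 = 396 events: about one standard error.

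**The case against.** - **Withdrawal is not defined.** It might be meant to include loss of contact, and the analysis plan, which is not available here, may say so. If it does, and dates it from the last reply, the point is closed for people who fall silent for good. The published rule does not say it.
- **Other sources exist.** Secondary outcomes may come from questionnaires, and participants keep a diary. Someone who stops texting but returns the 14-week questionnaire may be observed after all. This stands in part: the article does not say that the questionnaire dates a first slip in unanswered weeks, so the fix must allow for it without assuming it.
- **Complete non-responders may drop out.** Analyses use participants where data are available. That would still leave partial responders affected.
- **The pilot criteria are floors, not forecasts.** This stands. A reader might infer that the plan expects 20% of participants to answer under half the texts. It does not: the pilot passed, and randomisation normally requires two answered texts beforehand. Actual silence could be well below the shares assumed above.
- **The hazard ratio may not be biased at all.** This stands too. A reader might infer that the rule favours the shoes. That needs more silence in the intervention arm, which no figure supports, and the opposite pattern hides benefit.
- **Falls are different.** The weekly text shown asks only about slips, and the simulation covers slips only. For falls the same flaw depends on which instruments ask about them and are returned, and it is not quantified here.
- **Arm differences would be visible.** Missing data will be reported by arm. But the planned missing-data sensitivity analysis repeats only the primary analysis and defines non-response as no outcome data at all, so it does not repair the Cox model.

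**Conclusion.** The point holds for time to first slip. As written, the rule carries silent participants who have not withdrawn as slip-free through unobserved weeks, which is at odds with the primary model. Any such silence makes the Kaplan-Meier slip-free proportions too high: about 91% instead of 90% at week 14 if 20% of each arm is silent. Bias in the hazard ratio is possible rather than established. It is about 5-6% for a 10-point and 11-13% for a 20-point arm difference, in either direction, and essentially nil if rates are equal. All these sizes rest on assumed silence rates, permanent silence from a uniform time, and silence unrelated to slipping.

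The primary incidence rate ratio is not affected. This should be fixed before analysis because the cure is cheap, but it concerns secondary outcomes and does not threaten the trial's main conclusion.

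**What to change.** Replace the censoring sentence with a rule based on observation, for example:

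*Participants with no reported slip will be censored at the end of the last week covered by an answered text, or by a later returned questionnaire if it records dated slips. Participants with no reported fall will be censored at the end of the last period covered by a returned instrument that asks about falls. The same times will be used for the Kaplan-Meier curves and the Cox models.*

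Add a sensitivity analysis that censors at the first unanswered week. This addresses intermittent gaps, in which a first slip could be missed; the simulation tested only permanent silence. Report the proportion of texts answered by arm and week beside the hazard ratio, so that a reader can judge any difference.

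The cost is a few sentences and minor programming. The downside is slightly less person-time and marginally wider intervals. The new rule still assumes that falling silent is unrelated to slip risk given the covariates, so it removes the false slip-free time but not bias from informative silence.

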### Subgroup analyses

We will consider whether the intervention effect differs by gender and area of work by repeating the primary analysis including the factor and an interaction term between the factor and group allocation in the model.

### Missing data

The amount of missing data will be reported for each randomised arm, and we will also compare the baseline characteristics of participants who are included in the primary analysis to ensure that any attrition has not produced any imbalance in the groups in important variables. To account for any possible selection bias, a logistic regression will be run to predict non-response (no outcome data received during follow-up) including all variables collected prior to randomisation. The primary analysis will then be repeated including as covariates all variables found to be significantly predictive of non-response to determine if this affects the parameter estimates.

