## Discussion

Slips in workers are a major problem. If elimination of the potential slip risk is not possible, then one possible way to reduce the number of slips in the workplace may be to provide slip resistant footwear. Evaluation of slip resistant properties of footwear in slippery conditions is often undertaken using mechanical tests. The standard test method described in BS EN ISO 13287:2012 has been criticised and some have questioned its validity to predict pedestrian slip potential.^5 6^ It has been suggested that testing footwear under more lifelike conditions will more accurately assess the slip resistant properties of the footwear. The HSE have developed the ‘GRIP’ rating scheme. This scheme measures and categorises the level of wet slip resistance offered by the footwear. Footwear is rated on a scale of 1–5 stars, with 5 stars being the highest rating. The footwear used in this study has been assessed and achieved a 5-star rating. One potential limitation to the study is that the study uses unblinded, participant self-report outcome measures, so there is the possibility of reporting bias being introduced. In order to minimise the possibility of resentful demoralisation, the control group will be offered a free pair of trial shoes once their part in the study has ended. The SSHeW protocol aims to evaluate the effectiveness and cost-effectiveness of the 5-star rated footwear for the prevention of slips in the workplace. It will be the largest trial of its kind to date. Primary outcome data on the number of slips experienced will be collected weekly via SMS. This is a novel and efficient method of collecting these data. It is quicker, less burdensome and cheaper than participants posting a questionnaire back and, due to the regularity of data collection, minimises the chance of recall bias.

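### The planned missing-data sensitivity analysis keeps the assumption that missed weeks carry the same slip rate as answered weeks, so slip-related non-reply that differs by arm is untested

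*Protocol article*

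**What the plan says.** The primary outcome is the rate of self-reported slips "in the workplace over a 14-week period, as reported via weekly text messages" (Primary outcome measure), so each participant can contribute anything from 0 to 14 weekly reports.

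The primary model is a mixed effects Poisson or negative binomial regression. It handles incomplete reporting through exposure: "The number of weeks for which the participant provided weekly slip data and the number of hours worked in those weeks will be accounted for". It will also "adjust for pertinent baseline covariates such as gender, age, job role and baseline slip rate ascertained from the run-in period" (Statistical analysis of the SSHeW primary outcome).

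The Missing data section has three elements:

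- A description: "The amount of missing data will be reported for each randomised arm".
- A comparison of the baseline characteristics of participants included in the primary analysis.
- One sensitivity analysis, meant to deal with possible selection bias. In it, "a logistic regression will be run to predict non-response (no outcome data received during follow-up) including all variables collected prior to randomisation". Then: "The primary analysis will then be repeated including as covariates all variables found to be significantly predictive of non-response".

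Two other places bear on the point. The pilot progression criteria accept partial reply: 80% of participants giving at least 7 of 14 texts, and "Ninety per cent will respond to at least one postrandomisation text". The Discussion accepts that unblinded self-report brings "the possibility of reporting bias being introduced".

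**The concern.** The sensitivity analysis is aimed at participants who send nothing after randomisation. Someone who answers 3 of 14 texts counts as a responder, and the 11 missed weeks enter no model of missingness.

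The remedy applied also leaves the key assumption alone. Using the number of answered weeks as exposure takes the slip rate in missed weeks to equal the rate in answered weeks, given covariates and arm. Adding baseline covariates to a model fitted to the same answered weeks does not vary that assumption. Several likely candidates (gender, age, job role, run-in slip rate) are in the primary model already.

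Differential, slip-related reply is conceivable here. Participants know their allocation and report their own slips. The Participant recruitment section records that some pilot participants thought replies were needed only once the trial shoes had arrived. That was seen before randomisation, and the requirement for two run-in replies partly screens it out, but it shows that reply can depend on having the shoes. If people in one arm are less inclined to reply in weeks when they slip, the rate ratio is biased, and an unchanged refit could be read as reassurance it does not give.

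**Working it through.** **No figure to reproduce on this point.** The article gives no weekly reply rate and no figure for bias. The nearest stated figure is the 20% attrition allowance (Sample size). With 2200 × 0.8 = 1760 per arm and an assumed two-sided 5% level, power is 89.1% for 10% v 7% (stated 90%) and 81.7% for falls of 5.5% v 3.5% (stated 80%). Both reproduce, but the allowance covers lost precision, not bias.

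**How much missingness could lie outside the non-response model?** Take the pilot criteria at their limits: 80% give 7/14 weeks, 10% give 1/14, 10% give none.

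- Weeks answered: 0.80 × 0.5 + 0.10 × 1/14 = 0.407
- Weeks missed: 1 − 0.407 = 0.593, of which 0.10 comes from participants with no data
- Share of missed weeks from partial responders: (0.593 − 0.10)/0.593 = 83%

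This is the worst case that still passes the criteria, not a forecast.

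**Bias formula.** In each arm let m be the fraction of weeks missed and δ the slip rate in missed weeks divided by that in answered weeks. Then

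observed IRR = true IRR × [(1 − m_C) + m_C δ_C] / [(1 − m_I) + m_I δ_I]

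with I for intervention and C for control. Set true IRR = 1 and δ_C = 1. All values of m and δ are assumptions.

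| m_I | δ_I | Calculation | Observed IRR |
|---|---|---|---|
| 0.15 | 1.5 | 1/(0.85 + 0.225) | 0.93 |
| 0.15 | 2 | 1/(0.85 + 0.30) | 0.87 |
| 0.25 | 1.25 | 1/(0.75 + 0.3125) | 0.94 |
| 0.25 | 1.5 | 1/(0.75 + 0.375) | 0.89 |
| 0.25 | 2 | 1/(0.75 + 0.50) | 0.80 |

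If the control arm has the informative pattern instead, the ratio inverts: for m_C = 0.25 and δ_C = 1.5 it is 1.125. If m and δ are equal in both arms, numerator and denominator cancel.

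**Simulation.** The set-up was 2 × 2200 participants, 14 weekly overdispersed counts, about 10% with no data, and a negative binomial model with log(weeks answered) as offset, 40 replicates per scenario. Reply was 85% unless stated. Reply rates and dispersion are assumed.

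| Scenario | True IRR | Estimated IRR |
|---|---|---|
| Reply unrelated to slips, 85% in both arms | 1.0 | 1.02 |
| Reply unrelated to slips, 75% control v 90% intervention | 1.0 | 1.02 |
| Intervention replies in 70% of slip weeks | 1.0 | 0.84 |
| Intervention replies in 60% of slip weeks | 1.0 | 0.72 |
| 70% in intervention and 95% in control slip weeks | 1.0 | 0.76 |
| Intervention replies in 70% of slip weeks | 0.70 | 0.57 |

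The selective null results agree with the simple ratios 0.70/0.85 = 0.82, 0.60/0.85 = 0.71 and 0.70/0.95 = 0.74, given that the unbiased scenario itself came out at 1.02. Refitting with the baseline predictor of total non-response changed every estimate by less than 0.001. That predictor was simulated as unrelated to slipping, so the near-zero change partly follows from the set-up. In the selective scenarios mean weeks answered differed between arms by less than 0.1 (for example 10.65 v 10.61), because slip weeks are few, so a by-arm count of missing data would not have raised an alarm.

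**The case against.** A reader might infer more than the documents support.

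- **That the plan ignores missed weeks or cannot see arm differences.** It does neither. The amount of missing data is reported by arm, and the primary model accounts for weeks with data and hours worked. Where only the amount of reply differs by arm and is unrelated to slipping, the simulated estimate is the same as with equal reply. Arm-dependent non-reply is therefore not in itself a bias.
- **That leaving allocation out of the logistic model is a defect.** That model only selects extra covariates for a primary model that already contains allocation. Adding allocation to the selection step would not change the refit.
- **That at most 10% total non-response is expected, or that missed weeks are known to be the main loss.** The 90% figure is a pilot stop/go threshold. The 20% attrition allowance is not split into total and partial loss.
- **That the result will be tilted towards the shoes.** Nothing in the article fixes a direction. The illustrations put the informative pattern mainly on one arm by assumption.

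The design also limits the problem: two run-in replies are required, diaries are provided, controls are promised shoes, and the Discussion admits possible reporting bias. Finally, the article defers detail to a statistical analysis plan that is not shown and may contain further analyses.

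All of this stands, and it narrows the point. It does not remove it, because the article itself fixes the definition of non-response, the predictors and the purpose, and the method as written cannot serve that purpose.

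**Conclusion.** The point holds in a limited form. The stated refit adjusts for measured baseline predictors of total non-response. It leaves untested whether missed weeks differ in slip rate from answered weeks and whether that difference varies by arm, so its stated aim is too broad. Under no true effect and the assumed one-sided pattern (15-25% of intervention weeks missed, at 1.5-2 times the answered-week rate), the observed rate ratio is about 0.93 to 0.80. The lower end is a material part of the 30% relative reduction used in the sample size; the upper end is small. The direction reverses if the pattern lies in the control arm, and the bias vanishes if both arms are alike. These figures show sensitivity and do not estimate actual bias, since the documents give no weekly reply rates. The primary analysis can stand as planned; what should change is the sensitivity analysis and the claim made for it.

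**What to change.** 1. Keep the planned refit, but restate its purpose as adjustment for measured baseline predictors of total non-response.
2. Add a tipping-point sensitivity analysis of the primary model. Impute slips in missed weeks at δ times the fitted rate, vary δ separately by arm (for example 0.5 to 2), and report the δ pairs at which the conclusion changes. State whether the weeks of participants with no replies are imputed as well, and what hours are assumed for missed weeks.
3. Describe weekly reply rates by arm over the 14 weeks, so that readers can judge which δ pairs are plausible.

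This needs no new data collection and leaves the primary analysis unchanged. The cost is some programming and one additional sensitivity table.
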